### Follow-up

No adjuvant treatment will be used after surgery. All patients will be followed up every 3–6 months for up to 5 years after operation. Follow-up assessment will include: liver function (clinical assessment of Child’s grade, complete blood count, liver, and coagulation profile); recurrence (based on serum *α*-fetoprotein level, chest X-ray, and CT scan of abdomen with contrast); and quality of life (FACT-G questionnaires).

Patients with intrahepatic recurrence will be managed by laparoscopic re-resection for the LMH group or open re-resection for the OMH group when considered feasible. For patients in whom re-resection is not possible, thermal ablation, transarterial chemoembolization, or salvage liver transplant will be offered according to the decision of the multidisciplinary team.

### Participant timeline

Data accrual will be performed prospectively using wed-based electronic case-report forms (eCRFs) according to the protocol plan (*Table 1* and *Fig. 1*).

**Table 1 zrac166-T1:** Schedule of enrolment, interventions, and assessments of patients

	Study period					
	Enrolment	Allocation	Post-intervention			Close-out
**Time points**	− 1 month	0	Day 1, 3, 7, Day of discharge	Post-discharge 3, 6, 9, 12, 15, 18, 21, 24 months	Post-discharge 30, 36, 42, 48, 54, 60 months, unscheduled visits	Post-discharge 60 months
**Enrolment**						
Eligibility screening	X					
Informed consent	X					
QoL assessment	X					
Hepatectomy workup	X					
Allocation		X				
**Interventions**						
LMH group			X			
OMH group			X			
Protocol deviation			X			
**Assessments**						
Clinical evaluation including blood tests	X		X	X		
Radiological evaluation	X			X	X	
Postoperative evaluation including mortality and morbidity			X			
Serum *α*-fetoprotein					X	X
Tumour recurrence evaluation					X	X
QoL assessment					X	X
Patient survival evaluation					X	X
Study closure form						X

QoL, quality of life; LMH, laparoscopic major hepatectomy; OMH, open major hepatectomy.

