#### Secondary outcomes

These include 30-day, 90-day, and in-hospital mortality, postoperative complications, quality of life, time to functional recovery, 2-year overall survival, 5-year overall survival, and recurrence-free survival. Surgical stress-related cytokines serum interleukin 6 (IL-6) and immunosuppressive acidic protein (IAP) will be measured before surgery and on postoperative days 1 and 7. Measurement of IL-6 and IAP levels will be performed by immunoassay using commercially available kits (MILLIPLEX^®^ MAP Human Cytokine/Chemokine Magnetic Bead Panel, Merck Ltd, Rahway, NJ, USA).

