### Measurements

Intraoperative: operative time (measured from time of skin incision to wound suturing); blood loss; blood transfusion volumes and other blood products (platelet concentrate, fresh frozen plasma); intraoperative major events (hypotension for greater than 20 min and use of inotropes); and laparoscopic to open conversion. The conversion is defined as the change of surgical approach during the resection phase of major hepatectomy, when the operating surgeon encounters technical difficulty. Patients undergoing conversion will be included in the laparoscopic group and be analysed on an ‘intention-to-treat’ basis.

Postoperative: liver biochemistry and coagulation profile on postoperative days 1, 3, 7, and day of discharge; postoperative morbidities according to Clavien–Dindo classification^22^; 30-day, 90-day, and in-hospital mortality; length of ICU and hospital stay; hospital readmission (90 days after discharge); and time to functional recovery (defined as independently mobile at the preoperative level, sufficient pain control with oral medication alone, ability to maintain at least 50 per cent daily caloric intake, no intravenous fluid administration, and no clinical signs of infection)^23^.

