## Discussion

The aim of the AP-LAPO trial is to test the hypothesis that LMH is associated with reduced surgical stress and immunosuppression compared with OMH resulting in lower tumour recurrence rates and better survival.

OMH for HCC is associated with major morbidity of up to 40 per cent in high-volume centres^25–28^ as well as a high tumour recurrence rate. The 3-year recurrence rate has been reported to be greater than 50 per cent^7,29^ with most of these recurrences occurring in the liver remnant. Manipulation of the tumour during OMH along with postoperative immunosuppression induced by surgical stress have been suggested as factors that may increase risks of recurrence in the liver remnant^30^.

Recent series have proven the feasibility and safety of LMH for HCC^17^. The conversion and morbidity rates are around 10 per cent. Fewer wound and chest complications and shorter hospital stays are seen after LMH compared with OMH^10^. An animal study has shown that LMH results in less surgical stress and immunosuppression than OMH^9^. Theoretically, laparoscopic instrumentation causes less manipulation of the tumour that might limit cancer-cell dissemination, reducing tumour recurrence and prolonging survival. The reduced immunosuppression might also influence recurrence rates and survival in LMH. This theory is supported by a recent meta-analysis based on reconstructed time-to-event data^11^.

To date, only retrospective studies using propensity score matching have compared LMH and OMH^8,12^. Sample sizes were small (less than 40) in each matched group and the reported 2-year overall and recurrence-free survival were comparable between OMH and LMH. This trial aims to provide high-level evidence to see if there is added value of laparoscopic surgery in the treatment of patients with HCC.

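### Table 1 ends the morbidity and mortality evaluation at discharge; this does not match the 30- and 90-day mortality outcomes and leaves complications without a window common to both arms

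*Protocol article*

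**What the plan says.** - Table 1 (Participant timeline, Assessments) has a row "Postoperative evaluation including mortality and morbidity". Its only mark is in the column headed "Day 1, 3, 7, Day of discharge". The next column, "Post-discharge 3, 6, 9, 12, 15, 18, 21, 24 months", has no mark in this row.
- Secondary outcomes: "These include 30-day, 90-day, and in-hospital mortality, postoperative complications".
- Measurements repeats the mortality time points ("30-day, 90-day, and in-hospital mortality; length of ICU and hospital stay") and lists "postoperative morbidities according to Clavien–Dindo classification". It gives a grading system for complications but no start or end of counting. The same list includes readmission up to 90 days after discharge.
- Discussion, on published experience with the laparoscopic approach: "Fewer wound and chest complications and shorter hospital stays are seen after LMH compared with OMH".
- Blinding: none, for patients, surgeons or staff.
- Sample size: secondary outcomes serve only to generate hypotheses.

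**The concern.** A patient discharged before day 30 has no mark in this row at day 30 or day 90, although mortality at both points is a named outcome. For complications the text sets no window, so the schedule is the only guide a site has, and it stops at an event, discharge, that the document expects to come earlier in one arm. In an open-label trial the time of discharge is also decided by people who know the allocation.

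If a site counts to discharge, a wound infection on day 8 is recorded in a patient still in hospital but may go unrecorded in a patient already at home. Two arms with the same true complication risk would then show different recorded rates, in favour of LMH. At stake is the credibility of the complication comparison, and how complete the 30- and 90-day mortality data are.

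**Working it through.** **1. Schedule against outcomes.** The article states no figure on this point, so there is none to reproduce. The check sets the places side by side.

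| Outcome | Window in the text | Mark in the Table 1 row | Does length of stay change the window? |
|---|---|---|---|
| 30-day mortality | fixed, 30 days | to discharge | no; schedule falls short |
| 90-day mortality | fixed, 90 days | to discharge | no; schedule falls short |
| In-hospital mortality | to discharge | to discharge | yes, by definition |
| Complications | none stated | to discharge | yes, if the table is followed |
| Readmission | 90 days from discharge | not listed separately | its end date moves with the stay |

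**2. What else could capture later events.** Readmission is recorded, but a complication managed without readmission is not a readmission. Clinical evaluation is marked at months 3 to 24, but nothing says that it collects complications. The Follow-up section lists liver function, recurrence and quality of life, not complications.

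**3. Illustration of size.** From the document: a complication risk of 30% (Introduction, about 30% morbidity after open major hepatectomy, OMH) or 40% (Discussion, major morbidity up to 40%), and 165 patients per arm (Sample size). Assumed, because the document gives no such values: the same true 30-day risk p in both arms, exponential onset with parameter m of 4, 7 or 10 days truncated at day 30, stays (LMH v OMH) of 5 v 7, 6 v 9 or 7 v 12 days, and no capture after discharge.

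Recorded risk for stay L = p × F(L), with F(t) = (1 − e^(−t/m)) / (1 − e^(−30/m)).

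Worked case, p = 30%, m = 7, stays 6 v 9 days:
- F(6) = 0.5756 / 0.9862 = 0.584, so 17.5% is recorded in LMH.
- F(9) = 0.7235 / 0.9862 = 0.734, so 22.0% is recorded in OMH.
- Difference 4.5 points, ratio 0.80, although the true risks are equal.

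| Case | p | m | Stay LMH v OMH (days) | Recorded LMH v OMH | Difference (points) | Ratio |
|---|---|---|---|---|---|---|
| Smallest difference | 30% | 4 | 5 v 7 | 21.4% v 24.8% | 3.4 | 0.86 |
| Middle | 30% | 7 | 6 v 9 | 17.5% v 22.0% | 4.5 | 0.80 |
| Largest difference | 40% | 10 | 7 v 12 | 21.2% v 29.4% | 8.2 | 0.72 |

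Over all 18 combinations the difference runs from 3.4 to 8.2 points and the ratio from 0.72 to 0.87. With 165 per arm and a two-sided 5% test, the chance of a nominally significant result in favour of LMH is about 11% to 40%, against 2.5% in that direction without the artefact. A variant without truncation (risk 30%, stays of 5 v 8, 6 v 9 or 6 v 10 days, mean onset 4 to 14 days) gives about 3.5 to 5.5 points; its 6 v 9 day, mean 7 case is 17.3% v 21.7%.

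**4. Partial capture.** If a share c of post-discharge complications is recorded in both arms, the recorded risk is p × [F(L) + c × (1 − F(L))], and the difference shrinks by the factor (1 − c). With c = 0.5, 3.4 to 8.2 becomes 1.7 to 4.1 points.

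**5. After the fix.** With one day D from surgery in both arms, the difference due to the window is p × F(D) − p × F(D) = 0.

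**The case against.** The strongest case on the other side has five parts.

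- **Mortality.** A reader might infer that early deaths are under-counted in the LMH arm. The document does not support this. The 30- and 90-day windows are fixed and equal whatever the stay, patients are followed every 3–6 months for up to 5 years, and overall survival is analysed by Kaplan–Meier, which needs death dates. This part of the objection stands; what remains for mortality is the mismatch in the schedule.
- **Later capture exists.** Readmissions and the 3-month clinical evaluation would pick up some post-discharge complications, so bias is a risk and not an established fact. This stands. The offset is partial, because only readmissions are explicitly recorded, and that clock starts at discharge.
- **The table is weak evidence.** As it reads here, α-fetoprotein, recurrence, quality of life and survival are marked only from month 30, against the Follow-up section and a 2-year primary outcome. The table may be misprinted, or damaged when the text was read from PDF. This lowers confidence in any single cell. It does not supply a complication window, which the text also lacks.
- **A condensed article may leave the window to the full protocol.** Silence alone would be no finding. Here a schedule is stated, and as printed it falls short of outcomes that the article itself defines.
- **Stopping.** A reader might infer that the safety stopping decision under Interim analyses is distorted. Nothing ties serious adverse event reporting to this row, so that does not follow.

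**Conclusion.** The point holds in a limited form. As printed, Table 1 stops the morbidity and mortality evaluation at discharge. That contradicts the 30- and 90-day mortality outcomes, and it leaves complications with no stated window equal in both arms. If sites count complications only to discharge, the comparison is at risk of bias towards LMH. The direction rests on the document's own expectation of shorter stays.

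The size cannot be computed from the document. The figure of about 3 to 8 points depends wholly on assumed stays and onset times and on zero capture after discharge, so it is an illustration and not an estimate. It would be wrong to conclude that complication rates are biased, or that early mortality is. The outcomes concerned are secondary and hypothesis-generating, and 2-year recurrence-free survival is unaffected. The change is worth making because it is cheap now, and unrecorded complications may be hard to recover later.

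**What to change.** - State that Clavien–Dindo complications are counted from surgery to one fixed postoperative day in both arms, for example day 90, which matches the longest early mortality outcome.
- Mark the Table 1 row also at the 3-month post-discharge visit, and collect there complications and vital status through that day. This visit falls at or after about day 90 from surgery, because its clock starts at discharge. If a visit takes place early, confirm status at day 90 separately.
- Use this window for the between-arm comparison of complications.
- Check the other Table 1 rows against the Follow-up section at the same time.

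Cost: one more mark in the table and one more eCRF page at a visit that already takes place. Recorded complication rates will be slightly higher in both arms.

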### Sample size

Based on a reported 2-year recurrence-free survival rate of 72 per cent after OMH^12^ and an expected 88 per cent after LMH according to a previously reported series^8^, 150 patients need to be recruited to each arm to demonstrate a statistically significant difference with 80 per cent power at the 0.050 level of two-sided significant difference between LMH and OMH^24^. Allowing a 10 per cent dropout rate, 165 patients will be recruited in each arm. This sample size will allow detection of a reduction of 2-year tumour recurrence from 50 per cent in the OMH group to 30 per cent in the LMH group with a similar power and level of significance. Secondary outcomes will be interpreted for hypothesis-generating only.

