### Randomization

Preoperative randomization will be adopted on the day of admission. A total of 330 subjects will be allocated 1:1 to either the LMH group or the OMH group. The randomization schedule will be generated by the Clinical Trials Centre (CTC) of the principal investigator’s centre, prior to the start of the study. Stratified block randomization (block size of 10) will be used to ensure treatment allocation in equal proportions at each centre. The randomization list will be kept in a set of tamper-evident envelopes. The envelopes will be identical and sealed. The trial identifier with a sequential number will be printed on each envelope. Envelopes will be unsealed to reveal the allocation treatment 1 day prior to surgery.

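### The sample-size rates, power and number per arm do not agree: 72% v 88% at 80% power needs about 97 per arm, and 150 per arm gives about 94% power

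*Protocol article*

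**What the plan says.** The calculation is in the Sample size section of the Protocol article. The control rate is given as "Based on a reported 2-year recurrence-free survival rate of 72 per cent after OMH", and the experimental rate as "an expected 88 per cent after LMH according to a previously reported series". The result is "150 patients need to be recruited to each arm to demonstrate a statistically significant difference with 80 per cent power", tested "at the 0.050 level of two-sided significant difference between LMH and OMH". The section cites a reference for the calculation but does not name the formula.

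The dropout allowance comes after that figure: "Allowing a 10 per cent dropout rate, 165 patients will be recruited in each arm". The Randomization section confirms the total and ratio: "A total of 330 subjects will be allocated 1:1 to either the LMH group or the OMH group".

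A second scenario follows, 50% v 30% recurrence at 2 years. The section says that the same size will detect this difference too, "with a similar power and level of significance".

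The Statistical plan section names Kaplan–Meier estimation and the log rank test for the primary outcome.

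**The concern.** The article prints every input needed to check the number (two rates, a two-sided level, a power and a 1:1 ratio), and the printed result is about half as large again as those inputs produce. Detail left to a fuller document is not the issue, because the inputs and the result disagree on the page.

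At stake is the design target. If 88% is the intended laparoscopic rate, the trial has well over 80% power. If 80% is the intended power, the trial is sized for a smaller effect than the one printed. A reader cannot tell which effect the trial was built to detect. That matters here because the Discussion describes the earlier matched comparisons as small and as showing comparable survival, so an effect smaller than 16 points is plausible.

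**Working it through.** **Inputs** (Sample size and Randomization sections): p1 = 0.72, p2 = 0.88, two-sided α = 0.05 (z = 1.960), power 80% (z = 0.842), 1:1 allocation, 150 per arm before dropout.

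**1. Trying to reproduce 150: two proportions, pooled variance.** With p̄ = 0.80:

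n = [1.960·√(2·p̄(1−p̄)) + 0.842·√(p1(1−p1) + p2(1−p2))]² / (p1−p2)²

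= [1.960·√0.3200 + 0.842·√(0.2016 + 0.1056)]² / 0.16²

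= (1.1087 + 0.4665)² / 0.0256 = 96.9, so **97 per arm**.

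With continuity correction, n′ = (n/4)·[1 + √(1 + 4/(n·0.16))]² = 109.1, so **110 per arm**. The unpooled and arcsine versions each give 95.

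**2. Trying to reproduce 150: log-rank, 2 years of follow-up, proportional hazards.** HR = ln 0.88 / ln 0.72 = 0.389. The mean event probability is (0.28 + 0.12)/2 = 0.20.

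- Schoenfeld: events = 4(1.960 + 0.842)²/(ln 0.389)² = 35.2, and 35.2/0.20/2 = **88 per arm** (90 if events are first rounded up to 36).
- Freedman: events = [(1 + HR)/(1 − HR)]²·(1.960 + 0.842)² = 40.6, and 40.6/0.20/2 = **101.5, about 102 per arm** (103 if events are first rounded up to 41).

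**3. A deliberately unfavourable log-rank case.** Take the roughly 3-year accrual in the Trial status section, exponential hazards, and analysis on the last day of accrual with no further follow-up. This gives 120 (Schoenfeld) or 136 (Freedman) per arm. None of the variants in steps 1 to 3 gives 150.

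**4. Power at 150 per arm, 72% v 88%.** Power = Φ{[0.16·√150 − 1.1087]/√0.3072} = Φ(1.535) = **93.8%**. By other methods:

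| Method | Power at 150 per arm |
|---|---|
| Chi-squared | 93.8% |
| Fisher's exact | 92.3% |
| Log-rank, Schoenfeld (300 × 0.20 = 60 events) | 95.5% |
| Log-rank, Freedman | 92.6% |

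At 165 × 0.9 = 148.5 evaluable per arm, chi-squared power is 93.5%.

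**5. Second scenario, 50% v 30% recurrence.** The pooled formula gives 93.0 per arm for 80% power (102.8 with continuity correction). At 150 per arm, power is **94.6%** by chi-squared and 95.3% by Schoenfeld.

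**6. What 150 per arm does fit at 80% power.** With 72% in the open arm, power at 150 is 78.5% for 85% in the laparoscopic arm and 81.9% for 85.5%, by chi-squared. Schoenfeld gives 80.7% at 85%. So 80% power corresponds to about **72% v 85%**, with HR = ln 0.85/ln 0.72 = 0.49. This is for a comparison at 2 years or censored at 2 years.

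**The case against.** The strongest reply is that the slip is safe and changes nothing in the conduct of the trial. On the printed rates, every method above gives more than 80% power at 150 per arm, enrolment would not change, and no estimate or test would differ. That stands, and it limits the seriousness of the point. It does not make the printed figures agree.

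A second reply is that the cited reference may contain a step that cannot be seen here. That is possible. But the section states no continuity correction, design effect or interim adjustment of the significance level, and dropout is added after the 150.

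Several stronger readings are tempting and are not supported:

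- *That the power figure is the error.* The text shows only that three figures disagree. The slip could equally be the 88% or the 150.
- *That every method gives far fewer than 150.* In the unfavourable case in step 3, Freedman's formula gives 136. That is still short of 150, but not by a wide margin.
- *That the second scenario is a separate error.* Its power at 150 (94.6%) really is similar to that of the first (93.8%). It repeats the same departure from 80%.
- *That the dropout allowance is also wrong.* 165 is 150 × 1.10, while 150/0.9 gives 167. Two patients per arm is immaterial, and power at 148.5 is 93.5% against 93.8%.
- *That any null result or futility decision depends on this number.* The stopping condition in the Interim analyses section refers to the expected difference in recurrence, not to the sample size or nominal power. A null result would be read from its confidence interval.

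**Conclusion.** The rates, power and sample size in the Sample size section are mutually inconsistent. For 72% v 88% at two-sided 0.05 and 80% power, about 97 per arm are needed (about 110 with continuity correction, about 88 to 102 by log-rank with 2-year follow-up), not 150. At 150 per arm, power is about 94% for that contrast and about 95% for 50% v 30% recurrence.

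The error is conservative, so this is something that should be fixed rather than a threat to the trial's conclusions. Which of the three figures is the slip cannot be told from the text.

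The two-proportion results need only the printed inputs. The log-rank results assume proportional hazards and follow-up to 2 years. The 72% v 85% equivalence carries the same 2-year restriction. If the log rank test used all 5 years of follow-up, with exponential hazards, the hazard ratio detectable at 80% power would be nearer 0.63, or about 72% v 81% at 2 years (0.72^0.63 = 0.81).

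**What to change.** Name the formula used and reconcile the three figures.

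- **If the printed rates stand:** state that 150 per arm (or about 148 evaluable) gives about 94% power for 72% v 88% and about 95% for 50% v 30% recurrence. Add that 80% power corresponds to about 72% v 85% for a comparison at, or censored at, 2 years.
- **If 80% power was intended:** correct the expected laparoscopic rate, and give the second scenario its actual power.

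The cost is wording only. Enrolment stays at 330, and the dropout allowance can be left as it is.

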### Interim analyses

Patient recruitment status will be reviewed every 4 months in planned investigator meetings in which interim analyses will be carried out. If the accrual rate is slower than expected, the principal investigator and co-investigators will discuss the possible reasons and ways to improve the recruitment rate. The interim analyses will not be affected by the results. A data-monitoring group will consist of two independent, external experts who will be responsible for monitoring the progress of the study. If there are significantly more serious adverse events associated with either group after 1 year of commencement of the study, the trial will be terminated as decided by the principal investigator and the data-monitoring group. The same will be applied to the situation where the difference in tumour recurrence between groups is significantly less than expected. The final analysis of the trial will be carried out on an intention-to-treat basis.

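### The sample-size section gives two pairs of 2-year rates that cannot both hold, and its 150 per arm at 80% power does not follow from the pair it is based on

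*Protocol article*

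**What the plan says.** All references are to the Protocol article.

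- **Sample size, basis of N.** The control rate is a "reported 2-year recurrence-free survival rate of 72 per cent after OMH" and the experimental rate is "an expected 88 per cent after LMH according to a previously reported series". The two rates cite different references (12 and 8). From these the section derives 150 patients per arm for "80 per cent power at the 0.050 level of two-sided significant difference between LMH and OMH", raised to 165 per arm (330 in total) for dropout.
- **Sample size, added scenario.** The same number is said to detect, with similar power and significance level, a "reduction of 2-year tumour recurrence from 50 per cent in the OMH group to 30 per cent in the LMH group".
- **Discussion.** Of the two matched retrospective studies behind references 8 and 12, it says that each matched group had fewer than 40 patients and that "the reported 2-year overall and recurrence-free survival were comparable between OMH and LMH". On background risk after open surgery: "The 3-year recurrence rate has been reported to be greater than 50 per cent".
- **Interim analyses.** The trial may be terminated if "the difference in tumour recurrence between groups is significantly less than expected". No figure is attached to what is expected.
- **Statistical plan.** The primary comparison is a log-rank test on Kaplan–Meier RFS.

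**The concern.** The paragraph describes the same two arms at the same time point with two sets of figures. Since RFS fails on recurrence or death, it can never exceed one minus the recurrence proportion, and counting deaths only lowers it. The two sets therefore belong to different populations, and the text does not say which one the trial expects to enrol.

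Three things depend on the answer. The first is the event count: the log-rank test draws its information from events, and the two sets differ about twofold. The second is the target hazard ratio against which a null result would be read. The third is the benchmark for the stopping rule on tumour recurrence, which refers to an expected difference that the protocol never states as one number.

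The target effect also takes its open-surgery rate from one study and its laparoscopic rate from another, so differences between the two series in patients or follow-up may form part of the 16 points. Finally, the stated number per arm has to follow from the stated rates, power and significance level.

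**Working it through.** **Inputs.** From Sample size: RFS 72% v 88%; recurrence 50% v 30%; two-sided 0.05; 80% power; 150 per arm. From Discussion: fewer than 40 per matched group; 3-year recurrence above 50%. Assumption: proportional hazards for the hazard ratios (HR).

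**1. The plan's own figure.** The usual pooled formula for two proportions is

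n per arm = [1.960·√(2p̄(1−p̄)) + 0.842·√(p₁(1−p₁)+p₂(1−p₂))]² / (p₁−p₂)².

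- For 72% v 88%, p̄ = 0.80: (1.960×0.5657 + 0.842×0.5543)² / 0.16² = **97** per arm, or about 110 with continuity correction. On the log-rank scale it is 90 (Schoenfeld) to 103 (Freedman).
- For 50% v 30%, p̄ = 0.40: (1.960×0.6928 + 0.842×0.6782)² / 0.20² = **93** per arm, or about 103 with continuity correction.

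No two-sided 80% variant gives 150 for 72% v 88%.

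**2. Power at 150 per arm.** Power = Φ{[|p₁−p₂|√n − 1.960√(2p̄(1−p̄))] / √(p₁(1−p₁)+p₂(1−p₂))}.

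- 72% v 88%: Φ[(1.960 − 1.109)/0.5543] = Φ(1.54) = **93.8%**.
- 50% v 30%: Φ[(2.449 − 1.358)/0.6782] = Φ(1.61) = **94.6%**.

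The two powers are indeed similar to each other, but neither is 80%.

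**3. Incompatibility of the two pairs.** RFS ≤ 1 − recurrence.

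| Pair | Open | Laparoscopic | Implied limit | Difference | HR | Events by 2 years, 150 per arm |
|---|---|---|---|---|---|---|
| RFS | 72% | 88% | recurrence ≤ 28% and ≤ 12% | 16 points | ln 0.88 / ln 0.72 = 0.39 | 150×(0.28+0.12) = 60 |
| Recurrence | 50% | 30% | RFS ≤ 50% and ≤ 70% | 20 points | ln 0.70 / ln 0.50 = 0.51 | 150×(0.50+0.30) = 120 |

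The second row takes RFS at its upper limit, with no deaths before recurrence. Control-arm RFS differs by at least 72 − 50 = 22 points between the rows.

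**4. What 150 per arm detects at 80% power.** Solving the power formula in step 2 for p₂:

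- from 72%: about 85% (HR 0.49), with 150×(0.28+0.15) ≈ 64 events;
- from 50%: about 66% (HR 0.60), with 150×(0.50+0.34) = 126 events.

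**5. What the source studies could show.** With 40 per group, power for 72% v 88% is about 43% (42% with 39 per group). A comparable result in groups of that size does not exclude the effect.

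**6. Background rate, illustration only.** At a constant hazard, 3-year recurrence of 50% corresponds to 1 − 0.5^(2/3) = 37% at 2 years, so RFS of at most 63%. Conversely, RFS of 72% at 2 years becomes 0.72^1.5 = 61% at 3 years, so recurrence of at most 39%.

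**The case against.** The strongest reply is that the design effect is defined. Sample size names 72% v 88% RFS as the basis of N, and the recurrence sentence only adds a scenario that the same N would cover. Its claim of similar power is correct (93.8% and 94.6%), and the two pairs need nearly the same N (97 and 93). The incompatibility therefore changes neither the enrolment target nor the log-rank analysis. This stands. A reader might infer that the expected effect is undefined, but for the main calculation the text does not support that.

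A reader might also infer that the two source studies found no difference, or that neither saw a 16-point gap. The Discussion says only that results were comparable, in groups too small to settle the matter, and the within-study rates are not given. What the text supports is narrower: the two rates come from different small studies, which is weak support for the target.

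Nor does the background 3-year recurrence contradict the 72%. It refers to open resection for this cancer in general, whereas Eligibility criteria limit the trial to tumours up to 8 cm, Child A function and no radiological invasion of portal or hepatic vein branches. The 2-year conversion also needs a constant hazard.

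On the stopping rule, only the 50% v 30% pair is expressed as recurrence, so 20 points is the more literal reading. However, N rests on the 16-point RFS pair, and the rule itself gives no number.

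The reply does not rescue the recurrence sentence as a sensitivity scenario: it changes both endpoint and baseline without saying so. Nor does it explain the 150.

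**Conclusion.** The point holds as a fault in the stated figures. The two pairs of rates are arithmetically incompatible for the same arms, whatever the death rate. They imply HR 0.39 v 0.51 and about 60 v 120 events by 2 years at 150 per arm. Separately, 150 per arm does not correspond to 80% power for 72% v 88%: the power is about 94%, and the effect detectable at 80% is about 72% v 85%, or 50% v 66% if the lower control rate applies. The 16-point target is weakly justified, not refuted. In the stopping rule the expected difference has no stated value and could be read as 16 or 20 points.

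The trial is not underpowered for its stated target; on the stated inputs it has more power than claimed. The practical harm is moderate: the stated power is wrong, the target is ambiguous when a null result is read, and a termination rule lacks a fixed benchmark. The incompatibility needs no assumption beyond the usual definition of RFS. The powers and detectable rates compare 2-year proportions with complete follow-up of 150 per arm, and the HRs assume proportional hazards.

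**What to change.** Keep 330 patients and rewrite the paragraph:

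1. State one 2-year RFS assumption for the open arm, with a range (for example 50–72%), and one target on RFS expressed as a hazard ratio with the number of RFS events it needs.
2. Replace the 80% statement with what 150 per arm delivers: about 94% power for 72% v 88%, or the difference detectable at 80% power across the range (about 72% v 85%, HR 0.49, to 50% v 66%, HR 0.60).
3. Delete the sentence on recurrence of 50% v 30%, or restate it as RFS with deaths counted.
4. Say that the 72% and 88% come from separate small studies, and give the reason for the chosen target on that footing.
5. In Interim analyses, define the expected difference by reference to that single target, on the same endpoint.

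The cost is wording only. The published figures change, and the dependence of the detectable effect on the control rate becomes visible.
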